### Statistical analysis

We will use entropy balancing [35, 36] to control for differences between IG-PNP, CG-GP, and CG-UC in primary and secondary data. This method constructs balancing weights for each control observation such that the reweighted control groups match the covariate moments in the intervention group. The weights are based on patient characteristics (e.g. age, gender, region, type of insurance (compulsorily or voluntarily), costs of service utilization, mental comorbidity, and the Combined Comorbidity Index (CCI) [37] from ICD-10 for inpatient stays). The CCI is based on the ICD-10 codes belonging to the hospital stays, in order to take the severity of somatic comorbidities into account.

#### Effectiveness

We will use mixed linear models with fixed effects of group membership (IG-PNP / CG-GP / CG-UC) and further covariates, if necessary (e.g., in case of substantial inbalance between groups) to test the hypotheses regarding effectiveness. Primary medical practice affiliation will be modelled via random effects to adjust for possible clustering. Moderator analyses will be performed by adding interaction terms to the model. Results with *p* < .05 will be considered statistically significant.

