### Research questions, hypotheses and study design

#### Effectiveness

*Is treatment within the PNP program more effective compared to the treatment in the control groups (CG-GP, CG-UC) with regard to health related quality of life among patients with mental or neurological disorders (main research question)?*

i.1.) We expect higher scores of health-related quality of life for the IG-PNP compared to the control group CG-GP and to the control group CG-UC.

i.2.) We expect higher scores of functional health, lower illness-specific symptom burden as well as higher patient satisfaction for the IG-PNP compared to CG-GP as well as CG-UC.

*Which groups of patients benefit most from the PNP program?*

i.3.) We expect patients with chronic and severe focus diagnoses to benefit most from the PNP program. Accordingly, we expect chronicity (illness duration) and degree of severity to be significant moderators of the interaction effect. We will investigate additional moderators like gender, age, educational status, diagnoses and comorbidity.

We will conduct a prospective non-randomized controlled trial among patients to answer research questions related to effectiveness. We will include consecutively recruited patients belonging to the three groups (IG-PNP, CG-GP, CG-UC). We will measure health-related quality of life, patient-relevant symptom severity and satisfaction with care at baseline (t_0_, date of sick leave) and at 12-month follow-up (t_1_). Although randomized controlled trials could provide the best evidence in evaluation studies [28], we cannot randomize participants to the three groups for ethical and contractual reasons. In order to prevent the selection bias, we will recruit participants for all three groups in the same area in Germany (Baden Wuerttemberg). We will use entropy balancing to control for potential differences between intervention and control groups. No independent data monitoring committee to determine if the study should be modified or discontinued is necessary, because patients receive interventions irrespective of study continuation or participation. We will monitor and document study responses and discuss possible adaptions if necessary.

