### Outcome measures

Outcome measures are shown in Table 2.

**Table 2 Tab2:** Lists of outcome measures

Outcomes	Instruments
*Patient-related primary data*	
*Primary outcomes*	
Health-related quality of life	Short-form health survey (SF-36), mental component summary score [39]
*Secondary outcomes*	
Health-related quality of life	Short-form health survey (SF-36), physical component summary score [39], EuroQol-5D (EQ-5D) [40]
Depressive symptoms	Patient Health Questionnaire – Depression Module (PHQ-9) [41]
Anxiety symptoms	Patient Health Questionnaire – Generalized Anxiety Disorder Module (GAD-7) [42]
Somatoform symptoms	Somatic Symptom Scale – 8 (SSS-8) [43]
Alcohol consumption	Alcohol Use Disorders Identification Test (AUDIT) [44]
Schizophrenic symptoms	Eppendorfer Schizophrenia Inventory – Short Version (ESI-K) [45]
Adjustment disorder-symptoms	Adjustment Disorder-New Module 20 (ADNM-20) [46, 47]
Physical and psychological impact of multiple sclerosis	Multiple Sclerosis Impact Scale (MSIS-29) [48, 49]
Patient satisfaction with outpatient care	Satisfaction with ambulatory care (ZAPA) [50]
*Patient-related secondary data*	
*Primary outcomes*	
Direct costs caused by outpatient and inpatient service utilization and medication within one year following diagnosis	Claims data about outpatient and inpatient service utilization and medication
*Secondary outcomes*	
Indirect costs caused by productivity losses	Days of incapacity to work and sick pay
Level of detail of depression diagnoses	Claims data about diagnoses (specific: F32.0-F32.3, F33.0-F33.4; unspecific: F32.8, F32.9, F33.8, F33.9)
*Health care provider-related primary data*	
Aspects of the PNP program - access - reasons for participation - barriers to participation - advantages and disadvantages of participation - differences in health care - appropriateness of compensation - organizational aspects - interprofessional cooperation - evaluation and use of contract components	Questionnaire on structure and process quality of the PNP program, in-house development based on - qualitative interviews with selected health care providers - a questionnaire from another project (see [51])

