### Sample size calculation

The sample size was calculated for being able to detect a clinically relevant effect regarding the primary outcome health-related quality of life (SF-36) between IG-PNP and control groups CG-GP and CG-UC. Meta-analyses [19, 21, 32] calculated small to moderate effect sizes for collaborative care models. According to Cohen, a small to moderate effect size is defined as d = 0.30 [33]. Given an expected correlation of *r* = 0.4 between outcome at baseline and at follow-up, we will need *n* = 441 patients (*n* = 147 per group) to detect this effect with α = 0.05, power of 0.80 and without the random effect of health care providers offices [34]. Given an expected intraclass correlation of *p* = 0.10 and 100 health care providers in each group, we multiplied the necessary sample size with the design effect of DEF = 1.047 (1 + (147/100–1)*0.10) in consideration of random effects. Consequently, we need to include *n* = 153 patients per group (460 patients in total) in the analyses. We plan to overrecruit by 16.5% to compensate losses of statistical power through possibly different group sizes (IG- PNP ≈ 27%, CG-GP ≈ 22%, CG-UC ≈ 51%) with an allocation ratio of 2.33. Accordingly, we aim to include 536 patients in the analyses. Based on experiences, we expect a response rate of 7% for baseline. We expect dropout rates 40% for follow-up assessments. Consequently, we plan to contact *n* = 12,800 patients to receive data from *n* = 538 patients. We will perform dropout analyses for both study dropout and intervention dropout.

For analyzing direct and indirect costs (ii) and level of detail of diagnoses (iii), we will use complete secondary data from all patients meeting the inclusion criteria in 2015. Because of the exploratory approach, we did not conduct a formal sample size calculation for the evaluation of structure and process quality (iv).

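### The sample size counts on adjusting for baseline SF-36, but the primary model does not guarantee that adjustment

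*Protocol article*

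**What the plan says.** Table 2 of the protocol article gives the primary outcome for the patient survey as "Short-form health survey (SF-36), mental component summary score [39". It is measured at t0 (date of sick leave) and at t1, 12 months later.

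The section Sample size calculation takes a standardised difference of 0.30 as its target. Its assumption about the repeated scores reads: "Given an expected correlation of *r* = 0.4 between outcome at baseline and at follow-up". The size that results is 147 per group, 441 in all, for a 5% significance level and 80% power, before any allowance for clustering by practice.

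Under Statistical analysis, the paragraph on effectiveness describes a linear mixed model with group as fixed effect, practice as random effect, and "further covariates, if necessary (e.g., in case of substantial inbalance between groups". It mentions neither the t0 score nor a time term.

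Entropy balancing is planned for the primary data too. Its covariates are given as examples (among them demographics, region, utilisation costs, and mental and somatic comorbidity), and SF-36 at t0 is not one of them.

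Under Research questions, hypotheses and study design, the article expects chronicity and severity "to be significant moderators of the interaction effect", without saying which interaction is meant.

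**The concern.** The sample size treats the gain from the t0 score as certain, while the model description makes every covariate optional. The trigger is an imbalance that someone must judge to be substantial, with no threshold given, so the form of the primary model would be settled after looking at the data.

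Imbalance is also the wrong criterion for this covariate. The precision gained from a correlation of 0.4 is the same whether or not the groups differ at t0.

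Bias is at stake as well. Patients choose their own programme, and the Discussion concedes possible selection bias. The t0 value of the primary outcome is then an obvious measured confounder, and a difference too small to count as substantial could stay in the comparison.

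**Working it through.** **Inputs** (Sample size calculation): d = 0.30; r = 0.4; α = 0.05, sidedness not stated and taken as two-sided; power 0.80; design effect 1.047; 536 analysed; shares 27% / 22% / 51%.

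**1. Reproducing 147 per group.** n per group = 2(1.960 + 0.8416)² / 0.30² × f, where f is the variance factor of the analysis.

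| Analysis | f | n per group |
|---|---|---|
| t1 score adjusted for t0 | 1 − 0.4² = 0.84 | 146.5, so 147 |
| t1 score alone | 1 | 174.4, so 175 |
| Change from t0 to t1 | 2(1 − 0.4) = 1.2 | 209.3, so 210 |

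One-sided tests give 138 (t1 alone) and 116 (adjusted). Of these variants only two-sided testing with baseline adjustment gives 147. The article prints no formula, so the factor 0.84 is an inference, but the match is exact.

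**2. Power at the stated size if t0 is left out.** Power = Φ(0.30 / SE − 1.960), with SE = √(f × 2/n).
- n = 147, f = 0.84: 0.80
- n = 147, f = 1: 0.73
- n = 153 with design effect 1.047: 0.80 adjusted, 0.73 unadjusted

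The residual variance without t0 is 1/0.84 = 1.19 times as large.

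**3. Power at 536 analysed.** The group sizes are 0.27 × 536 = 144.7, 0.22 × 536 = 117.9 and 0.51 × 536 = 273.4. SE = √(f × 1.047 × (1/n₁ + 1/n₂)).

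| Contrast | with t0 | without t0 |
|---|---|---|
| IG-PNP vs CG-GP | 0.73 | 0.66 |
| IG-PNP vs CG-UC | 0.88 | 0.81 |

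These figures ignore the variance cost of the entropy weights.

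**4. Size needed without t0.** The design effect is 1.047 as stated, or 1 + (175/100 − 1) × 0.10 = 1.075 if recomputed. Then 175 × 1.047 = 183 and 175 × 1.075 = 188 per group. Three groups with 16.5% over-recruitment give about 640 to 657 analysed, against 536 planned.

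**5. Bias carried to t1.** With equal SDs at t0 and t1, an unadjusted t1 contrast carries r times the residual t0 difference. The t0 differences are assumed, since the article gives none:
- 0.1 SD: 0.4 × 0.1 = 0.04 SD, 13% of the 0.30 target
- 0.2 SD: 0.08 SD, 27%
- 0.3 SD: 0.12 SD, 40%

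**The case against.** The strongest reply is that this is an article, and the exact right-hand side of a model is normally left to the full protocol or the analysis plan. Silence about the t0 score does not show that it will be omitted, and the correlation in the sample size suggests that it is meant to be used. That stands as far as silence goes. But the article is not merely silent: it states an inclusion rule, and the rule does not deliver what the calculation assumes.

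A reader might infer that baseline differences in quality of life will go uncorrected. The text does not support this. A large difference is just what would trigger adjustment, and the balancing list is open-ended and already holds variables plausibly related to mental health. Correction is possible but not guaranteed.

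A reader might also infer that the interaction mentioned in the hypotheses is group by time, or that t0 and t1 will be stacked with only a group term. The phrase is undefined, and no section proposes a stacked model. A group-by-time model analysed as change would not rescue the figure anyway: it needs 210 per group, and 147 would give power 0.65.

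Finally, the power losses are a worst case in which t0 is never used. Even then power against CG-UC stays above 0.80. Against CG-GP it is already 0.73 with t0 in the model, because the groups are unequal; that shortfall is a separate issue.

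**Conclusion.** The concern holds as an inconsistency within the protocol article. The stated 147 per group depends on adjusting for t0 SF-36, and the stated model leaves that adjustment to an undefined, data-driven judgement. If it is not made, the cost is about 7 percentage points of power at the planned size (0.80 to 0.73 per group of 147; 0.73 to 0.66 against CG-GP; 0.88 to 0.81 against CG-UC), together with possible bias of 0.04 to 0.12 SD.

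The power figures assume two-sided testing, r = 0.4 as stated and no loss from weighting. The bias range assumes t0 differences of 0.1 to 0.3 SD that survive both balancing and the imbalance rule. It is an illustration, not a forecast.

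**What to change.** In the effectiveness paragraph under Statistical analysis, state that the t0 SF-36 mental component score is always a covariate in the model for the t1 score, whatever imbalance is observed, alongside the practice random effect and the entropy weights. The group coefficients at t1 are then the effects of interest.

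Align the moderator hypothesis with that model by defining the interaction as group × moderator.

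The cost is wording only. The t0 score is already collected, and the stated sample size needs no change on this account. The change should be made before outcome data are examined, since its purpose is to take the choice of model out of the data.

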#### Cost comparison analysis

We will perform comparisons between IG-PNP and control groups (CG-GP / CG-UC) using generalized linear mixed models. Direct and indirect costs will be considered.

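### A random practice intercept in the weighted mixed model does not keep the exact match that entropy balancing creates, so some measured confounding can return in the primary contrast

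*Protocol article*

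**What the plan says.** In the Protocol article, Statistical analysis, entropy balancing is the method for controlling group differences in both the primary and the secondary data. It "constructs balancing weights for each control observation such that the reweighted control groups match the covariate moments in the intervention group".

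The Effectiveness subsection then fixes the outcome model: a linear mixed model with fixed effects of group. On clustering it says: "Primary medical practice affiliation will be modelled via random effects to adjust for possible clustering". Further covariates may be added where needed, with marked imbalance between groups as the example. Costs are compared "using generalized linear mixed models" (Cost comparison analysis).

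The Sample size calculation supplies the clustering figures ("Given an expected intraclass correlation of *p* = 0.10 and 100 health care providers in each group"), the target ("a small to moderate effect size is defined as d = 0.30") and the baseline correlation ("Given an expected correlation of *r* = 0.4 between outcome at baseline and at follow-up").

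The article does not say at which level, or on what scale, the weights enter the models.

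**The concern.** Balancing weights affect the result only if the outcome model uses them, and the mixed models are the only models named for the hypotheses on effectiveness and costs. The two choices do not fit together without a further step. Exact balance belongs to the weights as constructed; a model with a random practice intercept applies different effective weights.

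Patients choose their own program, and the Discussion names entropy balancing as the (partial) control for selection bias. If part of the match is lost, the primary contrast keeps some of the measured confounding, in the direction of the original self-selection.

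**Working it through.** **1. The plan's own figures.** Inputs from the Sample size calculation: d = 0.30, r = 0.4, α = 0.05 (taken as two-sided; not stated), power 0.80.

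- n per group = 2 × (1.960 + 0.842)² × (1 − 0.4²) / 0.30² = 2 × 7.85 × 0.84 / 0.09 = 146.5, so 147, as stated.
- Design effect = 1 + (1.47 − 1) × 0.10 = 1.047, as stated. 147 × 1.047 = 153.9 (stated 153). 441 × 1.047 = 461.7 (stated 460). These small differences do not matter here.
- 460 × 1.165 = 535.9, so 536, as stated.
- Shares of 27%, 22% and 51% of 536 give about 145, 118 and 273 patients. With 100 practices per group that is 1.45, 1.18 and 2.73 patients per practice.

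**2. Effective weights.** Let λ be the ratio of practice variance to residual variance. At the planned intraclass correlation, λ = 0.10 / 0.90 = 0.111. With patient-level weights w, the weight used for the group contrast is

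w / (1 + λ × sum of w in the practice).

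Illustration for two single-patient practices with w = 1 and w = 4:

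- λ = 0.111: 1/1.111 = 0.90 and 4/1.444 = 2.77, so the ratio of 4 becomes 3.1.
- λ = 0.39: 1/1.39 = 0.72 and 4/2.56 = 1.56, so the ratio becomes 2.2.

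As λ grows, all such weights tend to 1/λ, which is the unweighted control group. Balance is therefore exact at λ = 0. For λ above 0 the calculations below show part of the raw imbalance returning, in its original direction.

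**3. Size.** Assumed, because the article gives no values: seven independent covariates, equal shifts, weights scaled to mean 1, separate practices in each group, no true effect. With equal effects aligned with the shift, raw confounding = √7 × shift × √R². Bias = raw confounding × share returned. The runs below had 800 replicates each, with λ estimated from the weighted data and no covariates in the model. Pairs are against CG-GP / CG-UC.

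| Shift (SD) | R² | Raw confounding (SD) | Share returned | Bias (SD) | Estimated λ | False positives |
|---|---|---|---|---|---|---|
| 0.10 / 0.13 | 0.16 | 0.11 / 0.14 | 16% / 10% | 0.02 / 0.01 | 0.17 | – |
| 0.15 / 0.20 | 0.16 | 0.16 / 0.21 | 17% / 16% | 0.03 / 0.03 | 0.22 | – |
| 0.25 / 0.33 | 0.16 | 0.26 / 0.35 | 27% / 25% | 0.07 / 0.09 | 0.39 | 6% / 9% |
| 0.25 / 0.33 | 0.05 | 0.15 / 0.20 | 30% / 24% | 0.04 / 0.05 | – | 7% / 6% |

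(– = no figure for these runs.) The true λ was 0.111, so the weighted fit overstates it. Further runs of the same design widen the share to about 7-30%. With the intraclass correlation held at 0.10 the share is about 2-16%. At moderate imbalance and R² 0.16, false positives were 3-5%. The simulation error of a 5% rate with 800 replicates is √(0.05 × 0.95 / 800) = 0.8 percentage points, so the 6% entries cannot be told from 5%.

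**4. Sensitivity to what is not given.** A separate calculation took a total covariate shift of 0.25 to 1.25 SD. With separate practices and weakly clustered covariates it gave 5-16% at the fixed intraclass correlation and 12-37% when it was estimated. If covariates cluster strongly by practice and practices are shared between groups, the share reaches about 60%.

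**5. The alternatives.** Weighted regression without the random intercept, same weights: bias within 0.01 SD. Weighted mixed model with all balanced covariates added: no linear confounding returns, and simulated bias is within 0.015 SD.

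**The case against.** - **The implementation is not stated.** A full protocol or analysis plan may settle how the weights enter. If a single-patient practice's weight were entered at practice level, its contribution would be w/(1 + λ), proportional to w, and balance would be kept for such practices. This stands as a limit: the result holds for patient-level weights, not for every software treatment.
- **The plan already allows covariates.** Adding all balanced covariates removes the linear bias. Sizing with r = 0.4 also presupposes adjustment for the baseline score, so a model without covariates is not quite the one the study was sized for. This stands too, but the clause is conditional. An analyst who looks at the weighted balance table will see an exact match and may add nothing, while the model works with other weights.
- **The higher range needs an inflated variance ratio.** True, but 0.10 is a planning value, and the stated model would estimate the variance from the weighted data unless it were fixed.

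A reader might infer that a fixed share of the confounding, around a third, returns under this plan; that the p < .05 rule generally loses its error rate; or that the cost contrast is biased to the same degree. The article supports none of these. It gives no imbalance, weight spread or covariate clustering; error rates exceeded 5% only at the larger assumed imbalance; and the cost evidence is a few linear runs at claims size, whereas the plan names generalized models and gives no practice sizes for those data.

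**Conclusion.** The point holds in a limited form. With patient-level weights, the random practice intercept gives up part of the covariate match, and the text does not ensure that anything restores it. Under the assumed imbalances the bias in the primary contrast is about 0.01 to 0.09 SD, or 3-30% of the target d = 0.30 (0.01/0.30 and 0.09/0.30). The lower end is negligible; the upper end would matter for a small-to-moderate effect. Which end applies depends on the actual imbalance, R², weight scaling, covariate clustering and sharing of practices. For the cost models the mechanism is the same in kind, but its size is not established.

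**What to change.** In the Effectiveness subsection, adopt one of two wordings:

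- **Keep the weighted mixed model** and always include every balanced covariate together with baseline MCS, without a condition on observed imbalance. Cost: a few more model terms.
- **Estimate the group effects by entropy-weighted regression** with practice-clustered, small-sample-corrected standard errors, and keep the mixed model as a sensitivity analysis. Cost: a small loss of efficiency; the empirical SD of the estimate rose by about 0-7% in simulation.

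In both cases, state how the weights enter and are scaled, and report balance under the model's effective weights as well as under the raw entropy weights. Make the same change in the Cost comparison analysis. No new data are needed.

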#### Cost comparison analysis

We will perform comparisons between IG-PNP and control groups (CG-GP / CG-UC) using generalized linear mixed models. Direct and indirect costs will be considered.

#### Level of detail of diagnoses

To analyze the level of detail of diagnoses, we will conduct exploratory analyses, i.e. descriptive trend analysis, for specific diagnoses in the 12-month follow-up period stratified according to IG-PNP and CG-GP or CG-UC.

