Requirements for participation (patients)	- free choice of health care providers with a license in Baden-Wuerttemberg	- minimum time of participation: 12 months - commitment to seek help from GPs enrolled in the program only - commitment to seek help from GPs first (exception: emergencies, gynecologist, ophthalmologists, pediatricians)	- enrolled in the general practitioners program and the specialist program - minimum time of participation: 12 months - commitment to seek help from health care providers enrolled in the program only - commitment to seek help from GPs first (exception: emergencies, gynecologist, ophthalmologists, pediatricians)
Requirements for participation (health care providers)	- license in Baden-Wuerttemberg	- license in Baden-Wuerttemberg - GP	- license in Baden-Wuerttemberg - psychotherapists and specialists in psychiatry, neurology, psychotherapy, or psychosomatic medicine - enrolment in at least one of three modules: psychiatry, neurology, psychotherapy
Role of GPs	- diagnosis, treatment, referral to specialists	- diagnosis, treatment, referral to specialists - guiding through care: structured coordinating and communication to specialists care and merging results of medical examinations	- diagnosis, treatment, referral to specialists - guiding through care: structured coordinating and communication to specialists care and merging results of medical examinations
All providers			
Compensation and diagnoses	- health care services for patients with specific and unspecific diagnoses in accordance with ICD-10 are billable	- health care services for patients with specific and unspecific diagnoses in accordance with ICD-10 are billable - fee for cooperation with specialists	- health care services for patients with predominantly specific diagnoses in accordance with ICD-10 are billable (e.g., for depressive disorders, only the specific codes F32.0-F32.3, F33.0-F33.4 are billable; the unspecific codes F32.8, F32.9, F33.8, and F33.9 are not billable) - fee for cooperation with specialists and GPs
Social service	- social service of the AOK Baden Wuerttemberg	- more structured cooperation between health care provider and social service of the AOK Baden Wuerttemberg	- more structured cooperation between health care provider and social service of the AOK Baden Wuerttemberg

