Quality management	- mandatory continuous training courses	- mandatory continuous training courses - participation in quality circles on drug therapy (once per quarter) for GPs	- mandatory continuous training courses - participation in quality circles on drug therapy (once per quarter) for GPs (optional for specialists)
Psychotherapy			
Differences in compensation	- higher payment of regular sessions compared to preparatory sessions (2–4 preparatory sessions)	- higher payment of regular sessions compared to preparatory sessions (2–4 preparatory sessions)	- higher payment for first sessions (acute / initial care = 10/20 sessions) compared to long-term therapy and compared to usual care - higher payment for group psychotherapy compared to usual care - collective incentives for saving sickness benefits
Organization	- review process for approval of long-term psychotherapy	- review process for approval of long-term psychotherapy	- no review process for approval of long-term psychotherapy
Treatment content	- Cognitive Behavioral Therapy - Psychodynamic Psychotherapy - Psychoanalytic therapy - Neuropsychological therapy - Hypnosis - Eye Movement Desensitization and Reprocessing (EMDR)	- Cognitive Behavioral Therapy - Psychodynamic Psychotherapy - Psychoanalytic therapy - Neuropsychological therapy - Hypnosis - Eye Movement Desensitization and Reprocessing (EMDR)	- Cognitive Behavioral Therapy - Psychodynamic Psychotherapy - Psychoanalytic therapy - Additional treatment methods depending on diagnosis: ○ Neuropsychological therapy ○ Hypnosis ○ Eye Movement Desensitization and Reprocessing (EMDR) ○ Systemic psychotherapy ○ Biofeedback ○ Interpersonal therapy
Additional guidelines on accessibility	/	/	- for acute cases: initial session within 3 days; start of psychotherapy within 7 days after established diagnosis - for initial treatment: start of psychotherapy within 4 weeks after established diagnosis
Psychiatry			
Additional compensation	/	/	- additional supplements for → counselling (e.g. supportive counselling for patients with depression) → provision of technical equipment → prescription of discounted medication → collective incentives for the prevention of hospital admissions
Additional guidelines on accessibility	/	/	- limit of waiting time up to 30 min - for acute cases: first doctor’s appointment within the same day
Neurology			

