#### Level of detail of diagnoses

Is the *amount of specifc diagnoses higher during the treatment process in the PNP program compared to the control group CG-GP and to the control group CG-UC?*

iii.a.) We expect health care providers to submit a higher percentage of specific depression diagnoses (with determination of the degree of severity) in proportion to unspecific depression diagnoses for patients in IG-PNP to the statutory health insurance compared to CG-GP as well as CG-UC.

In order to determine the amount of specific diagnoses, we will also use retrospective secondary data from 2014, 2015 and 2016. Therefore, we will use a trend analysis of diagnoses, stratified according to the intervention and control groups.

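### Hypothesis iii.a predicts a higher share of specific depression diagnoses in IG-PNP, but the plan gives only a descriptive trend, with no between-group estimate or interval to support or reject it

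*Protocol article*

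**What the plan says.** Under Research questions, hypotheses and study design (Level of detail of diagnoses), hypothesis iii.a expects providers of IG-PNP patients to "submit a higher percentage of specific depression diagnoses (with determination of the degree of severity) in proportion to unspecific depression diagnoses", compared with CG-GP and with CG-UC. The design sentence that follows says "we will use a trend analysis of diagnoses, stratified according to the intervention and control groups", using claims data from 2014, 2015 and 2016.

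Table 2 ranks the level of detail of depression diagnoses as a secondary outcome of the secondary data. It defines the outcome by code: "Claims data about diagnoses (specific: F32.0-F32.3, F33.0-F33.4; unspecific: F32.8, F32.9, F33.8, F33.9").

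The Level of detail of diagnoses paragraph under Statistical analysis fixes the method: "we will conduct exploratory analyses, i.e. descriptive trend analysis, for specific diagnoses in the 12-month follow-up period", stratified by group. The opening of Statistical analysis announces entropy balancing for primary and secondary data alike.

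Table 1 (Compensation and diagnoses) states that in the PNP program "the unspecific codes F32.8, F32.9, F33.8, and F33.9 are not billable", whereas services under specific and unspecific diagnoses are billable in both control conditions.

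**The concern.** A hypothesis with a direction and two named comparators needs an analysis that returns a difference and its uncertainty. The plan states a method for iii.a, and that method returns neither. Whatever the curves look like, the report will have to judge by eye whether iii.a was met.

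The eye has little to go on. One patient can contribute many depression codes over 12 months, and patients of one practice share a coder, so the codes are not independent. The trend is also confined to follow-up. Patients choose their own contract status, and a coding difference that existed before the index sick leave would look the same as one that arose afterwards.

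At stake is one of the study's four evaluation aims. A visible gap could be reported as more accurate diagnosis under the PNP program when the plan gives neither its precision nor a way to set it against the contract's billing rule.

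**Working it through.** **Step 1. Match of aim and method.** The protocol article gives:

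| Aim | Hypothesis stated? | Analysis stated |
|---|---|---|
| (i) Effectiveness | Yes, directional | Mixed linear models, practice as random effect, p < .05 |
| (ii) Costs | Yes, directional | Generalized linear mixed models |
| (iii) Level of detail | Yes, directional, two comparators | Descriptive trend by group |
| (iv) Structure and process quality | Explicitly none | Descriptive |

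Aim (iii) is the only one that pairs a directional hypothesis with a purely descriptive method. The article declares an aim hypothesis-free only for (iv). There is no sample size, effect size or error rate for iii.a to reproduce.

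**Step 2. Error of a gap read off the trend.** Treating m codes per patient as independent understates the variance by 1 + (m − 1)ρ, where ρ is the correlation of codes within a patient. The document gives neither value, so both are assumed: m = 3 or 8, and ρ from 0.10 (borrowed from the practice-level intraclass correlation in Sample size calculation, which is for the SF-36) to 1 (each patient always coded alike).

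- ρ = 0.10: 1 + 2 × 0.10 = 1.2 and 1 + 7 × 0.10 = 1.7. The standard error is too small by √1.2 = 1.10 to √1.7 = 1.30.
- ρ = 1: 3 and 8. The standard error is too small by √3 = 1.73 to √8 = 2.83.

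Clustering by practice comes on top of this.

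**Step 3. What the billing rule alone can do.** Let q be the share of specific codes without the rule, and f the fraction of unspecific entries that the rule removes. If these are recoded as specific, the share becomes q + (1 − q)f. If they are dropped, it becomes q / (q + (1 − q)(1 − f)). Both q and f are assumptions.

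| q | f | Recoded | Dropped |
|---|---|---|---|
| 0.40 | 0.50 | 0.70 | 0.57 |
| 0.60 | 0.25 | 0.70 | 0.67 |
| 0.60 | 0.50 | 0.80 | 0.75 |
| 0.60 | 0.90 | 0.96 | 0.94 |
| 0.80 | 0.50 | 0.90 | 0.89 |

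Worked line: 0.60 + 0.40 × 0.50 = 0.80, and 0.60 / (0.60 + 0.40 × 0.50) = 0.75. No difference in diagnostic care or in contact frequency is needed.

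**Step 4. Are the data for a better analysis at hand?** The claims cover 2014 to 2016, and the sample for this aim is patients who meet the inclusion criteria in 2015. An index date at the start of 2015 leaves 12 months of earlier data, and one at the end of 2015 leaves 12 months of follow-up. Pre-index periods can therefore be shown for everyone. Weights are announced for the secondary data, and generalized linear mixed models are already planned for costs.

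**The case against.** The strongest reply is that nothing is hidden. The analysis is openly called exploratory, the outcome is secondary, and the data are complete for eligible patients, so stratified shares do inform a directional expectation. Entropy balancing may also be applied to them. Much of this stands: the defect is a mismatch between hypothesis and method, not a concealed failure to test. But the label sits in the analysis section while the directional expectation stays in the hypotheses. Complete data for one year's patients do not remove the uncertainty in a comparison meant to speak about the program.

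A second reply is that a share of submitted codes is the wrong unit and should be replaced by a patient measure. The documents do not support that. The hypothesis concerns what providers submit, so a code-level share fits it. How codes are aggregated can properly be left to a fuller plan. An outcome such as at least one specific code per patient would itself rise with contacts: at an assumed, independent 0.60 per contact it is 1 − 0.40² = 0.84 with two contacts and 1 − 0.40⁴ = 0.97 with four, while the code share stays 0.60.

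A reader might also infer that more billed contacts under the PNP program by themselves raise its share. They do not. If every patient has more contacts and coding is unrelated to their number, 0.60 stays 0.60. If only specifically coded patients have twice as many, it becomes 1.2 / (1.2 + 0.4) = 0.75. If only unspecifically coded patients do, it falls to 0.6 / (0.6 + 0.8) = 0.43. Table 1 describes payment rates for sessions, and the document gives no codes per patient by group, so neither the direction nor a size follows from it.

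**Conclusion.** The point holds for the mismatch. As written, the plan offers no between-group estimate or interval with which to support or reject iii.a, and any gap read off the trend lacks a valid error. That conclusion rests on the text alone. The standard-error factors in Step 2 (1.10 to 2.83) rest on assumed code counts and correlations and show only that the matter is not negligible.

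The billing rule limits what even a precise contrast could mean, because the contract does not pay for the very codes that form the comparison category. How far it moves the share is unknown. The figures in Step 3 are illustrations, not estimates.

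The primary outcomes are unaffected. For a secondary outcome with an openly exploratory analysis this is a change that should be made, not one on which the study depends.

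**What to change.** Keep the share of specific codes among submitted depression diagnoses as the measure, and say so in the analysis section, since the research question speaks of an amount and the hypothesis of a percentage.

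- Apply the entropy-balancing weights already announced for the secondary data.
- Report IG-PNP minus CG-GP and IG-PNP minus CG-UC, each with a 95% CI that allows for clustering within patient and practice. Either a binomial generalized linear mixed model, with the differences taken from averaged predictions, or a weighted binomial model with clustered errors will do. If each patient is assigned to one primary practice, as in the effectiveness analysis, clustering on practice also covers repeated codes within a patient.
- Show pre-index periods from the 2014 to 2016 data on the same trend.
- State beside the result that the codes defining unspecific are not billable in the PNP program, so a higher share may reflect the billing rule and not better diagnosis. Patients already enrolled before the index date may be subject to the rule then too, so the pre-index curve does not remove this explanation.

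If the analysis is to remain descriptive, reword iii.a as an exploratory question and drop the directional expectation.

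The cost is wording and a little more programming. No new data are needed.
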